# Safety and efficacy of PG102P for the control of pruritus in patients undergoing hemodialysis (SNUG trial): study protocol for a randomized controlled trial

**DOI:** 10.1186/s13063-019-3753-1

**Published:** 2019-11-28

**Keywords:** Uremic pruritus, Hemodialysis, PG201P

## Abstract

**Background:**

Pruritus in patients undergoing hemodialysis is a highly prevalent complication that affects quality of life. Several medications are currently used for the treatment of uremic pruritus, but these are not satisfactory. PG102P, which is prepared from *Actinidia arguta*, has an immune-modulating effect on pruritus. This trial is designed to assess the antipruritic effect of PG102P compared with placebo.

**Methods:**

This multicenter, randomized, double-blind, placebo-controlled clinical trial will include 80 patients undergoing hemodialysis. The patients will be randomized in a 1:1 ratio to a treatment group (PG102P 1.5 g/day) or a control group (placebo). The treatment will last for 8 weeks, followed by a 2-week observational period. During the observational period, all of the patients will maintain the antipruritic treatment previously used. The primary endpoint will be measured as the difference in visual analog scale between the groups before and after treatment. Secondary outcomes include serum levels of total immunoglobulin E, eosinophil cationic protein, potassium, calcium, phosphorus, intact parathyroid hormone, and blood eosinophil count between weeks 0 and 8. Kidney Disease and Quality of Life and Beck’s Depression Inventory questionnaires will be conducted. Safety assessments and any adverse events that occur will also be evaluated.

**Discussion:**

The SNUG is a clinical study that aims to investigate the antipruritic effect of PG102P to ameliorate itching in patients undergoing hemodialysis.

**Trial registration:**

Clinical Trials.gov, NCT03576235. Registered on 4 July 2018.

## Background

Pruritus is a common and distressing complication in patients with end-stage renal disease [1, 2]. A global cross-sectional study in 12 countries with more than 18,000 patients undergoing hemodialysis (HD) reported that 42% of patients experienced moderate-to-severe pruritus [3]. Pruritus is associated with impaired quality of life, sleep disturbance, depression, and increased risk of mortality [4].

The pathophysiologic mechanism of pruritus is largely unclear [5]. However, anemia, hypercalcemia, hyperphosphatemia, secondary hyperparathyroidism, and hypermagnesemia are known to be associated with uremic pruritus [6, 7]. Moreover, more than 60% of patients undergoing HD who do not have significant metabolic disorders also suffer from chronic pruritus [8].

A longitudinal study of uremic pruritus reported that changes in itching intensity more than 20% significantly improved quality of life in patients with moderate-to-severe itching symptoms [9]. However, treating patients with uremic pruritus is a challenge. Antihistamines, steroids, emollients, and phototherapy are currently used, but have not been thoroughly investigated. Adequate skin hydration is the cornerstone of antipruritic treatment because xerosis is common in patients undergoing HD. In a recent review article, gabapentin is recommended due to consistent successful results in several clinical trials [10–12], which included only 25 to 34 patients. In a recent study, oral antihistamines were used by 57% of clinicians as first-line treatment for uremic pruritus [13], but were no longer recommended in the latest reviews [14, 15]. Therefore, a novel therapeutic option is necessary to ameliorate uremic pruritus.

PG102P, which is prepared from *Actinidia arguta*, generally called hardy kiwifruit, contains an orally active immune-modulating activity through T helper 1/2 pathways [16] and by inducing regulatory T cells [17]. It shows an anti-inflammatory effect in various murine models, such as atopic dermatitis [18], allergic diarrhea [19], and asthma [20]. Therefore, we hypothesized that the immune-modulating property of PG102P would play a role in controlling itching. In this study (the SNUG trial) we aim to investigate the antipruritic effect of PG102P in comparison with placebo in 80 patients undergoing HD.

## Methods/design

### Study design

This is a multicenter, randomized, double-blind, placebo-controlled trial in which one group will be treated with PG102P (1.5 g/day) and the other with a placebo. It is an investigator-initiated clinical trial. The overall study algorithm is illustrated in Fig. 1. A superiority trial is planned to test the hypothesis that PG102P is effective in relieving pruritus for patients with end-stage renal disease undergoing HD. Nine tertiary university hospitals (Seoul National University Boramae Medical Center, Seoul National University Hospital, Seoul National University Bundang Hospital, Ewha Womans University Mokdong Hospital, Severance Hospital, Chungnam National University Hospital, Gachon University Gil Medical Center, Kyungpook National University Hospital, and Dongguk University Ilsan Hospital) will participate in the trial. It was retrospectively registered at http://www.clinical
trials.gov/ (NCT03576235). Patients aged over 19 years who have chronic pruritus despite conventional antipruritic treatment undergoing HD will be screened for the study participation. During the study period, antipruritic drugs which had been started before this study were administered in all of the study populations without changing the dosage of the drugs.

**Fig. 1 Fig1:**
[figure not shown]
Flow chart of the SNUG trial

### Inclusion criteria

The inclusion criteria include the following:
Age over 19 yearsPatients with adequate HD (a dialysis efficiency calculator, or Kt/V, score >1.2, 4 h of HD three times per week).Maintenance patients undergoing HD (>3 months) with chronic pruritusMean visual analog scale (VAS) score >4 for the last 5 days in the 14-day preobservation periodParticipants who were allowed to continue the antipruritic drug treatment at the same dosage and administration schedule as used at baseline throughout the study periodPatients who agreed to participate in this trial and provided written informed consent

### Exclusion criteria

The exclusion criteria are outlined below:
Intact parathyroid hormone >1000 pg/mL within 1 monthSerum potassium >7.0 mg/dLHIV antibody-positiveAspartate transaminase (glutamic oxaloacetic transaminase) or alanine transaminase (glutamic pyruvic transaminase) >3 times the upper limit of normalScheduled to have kidney transplantation within 3 monthsCancer history with current treatmentActive infection with current treatmentCurrent itching with dermatologic diseases other than uremic pruritusPregnancy, childbearing potential during the study period, or breastfeedingAllergy or hypersensitivity reaction to PG102PHistory of participating in another clinical trial within 2 months or planning to participate in another clinical trialNot eligible to participate in this trial as a decision of the researchers

### Randomization

Randomization will be performed by an independent statistician using a computerized random number generator through the block randomization method of SAS 9.3 software (SAS Institute, Cary, NC, USA). Eligible participants will be randomly assigned 1:1 to either a placebo group or a treatment group. All subjects eligible for selection/exclusion criteria at visit 2 (baseline visit, week 0) will be assigned to a group according to the allocation codes of the blocked randomization method. Each patient will be given a unique study number. An independent data manager who is not involved with the clinical practice or patient recruitment will create the randomization sequence. The practitioners, participants, outcome assessors, and statisticians will be kept blinded to treatment allocation throughout the trial. The randomization lists will be computer-generated and concealed from the investigators by an independent data manager not involved in the study. This information will remain confidential and will not be available to the researchers. In this trial, emergent unblinding is not applicable.

### Follow-up

The participants will visit the hospital seven times during the study: a screening visit (visit 1), visits during active treatment (visits 2, 3, 4, and 5), and a follow-up visit (visit 6). Each interval between visits is 2 weeks, except that between visits 4 and 5 (which is 4 weeks).

### Primary endpoint and measurement of itch

The primary endpoint is the change in VAS between visit 2 (week 0) and visits 3, 4, 5, and 6 (weeks 2, 4, 8, 10)—VAS change from baseline.

Itch severity will be measured by the patients using a VAS. A VAS consisting of a 10-cm horizontal line with 1-cm scale markings will be used. The patients will be asked to mark the intensity of their itch on the scale, with the strongest possible itch marked at the right end of the line (10 cm) and no itch marked at the left end (0 cm). The patients will be asked to mark the VAS value to record the worst degree of itch experienced during the previous day. Patients with an average VAS value of 4 or more for 5 consecutive days before visit 2 (week 0) will be enrolled. The average value of VAS measured 3 consecutive days before each visit (visits 3 to 7) will be used to evaluate itching.

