### Sample size calculations

The enrolled participants will be randomly divided into two groups by at a 1:1 ratio. Under the assumption of 2.1 cm (with a pooled standard deviation of 2.4 cm) in the mean change difference in VAS values between the PG102P and placebo groups in a preceding pilot study with 0.9 of power, two-sided, and 0.05 of alpha, 28 participants will be allocated to each group. Considering a dropout rate of 30%, 80 participants will be needed (40 participants per group).

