### Statistical analyses

Three analysis sets will be used for analyzing data. First, a safety analysis set will be applied to analyze safety evaluation parameters. Safety analysis will be performed for a group of subjects who have ingested at least one treatment after random assignment. Second, a full analysis set will be applied, which refers to the ideal set of subjects as close as possible to the principle of intentionality analysis (including all of the subjects randomized to enroll and receive at least one treatment). Third, a per-protocol set will be applied when all of the factors are in accordance with the research plan; patients show good compliance using 80–120% of the prescribed dose. All of the baseline variables must be available, and there must be no major violation of the test plan.

For the primary endpoint, the degree of change of the VAS averaged after treatment from baseline will be analyzed using the paired *t* test or Wilcoxon signed rank test in each group. The difference between the groups will be analyzed with the two-sample *t* test or Wilcoxon rank sum test. Additionally, an analysis of covariance will be conducted with adjustments for covariates. Similar to the primary endpoint, the same analyses will be performed for the secondary endpoints. For categorical variables, the McNemar test will be carried out to evaluate the change from baseline in each group.

Demographic and clinical characteristics will be reported in terms of mean ± standard deviation for continuous variables, or as frequencies and percentages for categorical variables. Differences between groups will be analyzed using the two-sample *t* test or Wilcoxon rank sum test for continuous variables and the χ^2^ test or Fisher’s exact test for categorical variables.

AEs and adverse drug reactions will be tabulated for each treatment group in accordance with the system organ class and preferred terms of the Medical Dictionary for Regulatory Activities. The AEs and adverse drug reactions will then be classified according to severity, seriousness, and causal relationship to the study drug. Intergroup comparisons will be conducted using the χ^2^ test or Fisher’s exact test.

A value of *P* < 0.05 will be considered statistically significant. All analyses will be performed using SPSS Statistics software (v21.0; IBM Corporation, Armonk, NY, USA).

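### The primary endpoint spans four visits, one of them after treatment ends, with no decisive visit or multiplicity rule, while the sample size assumes one comparison at 5%

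*Protocol article*

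**What the plan says.** Four places in the protocol article bear on what the primary comparison is.

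- **Primary endpoint and measurement of itch:** the endpoint is "the change in VAS between visit 2 (week 0) and visits 3, 4, 5, and 6 (weeks 2, 4, 8, 10". Each visit's value is the mean of the VAS over the three preceding days. No visit is ranked above another.
- **Abstract, Methods:** "The primary endpoint will be measured as the difference in visual analog scale between the groups before and after treatment". This is one difference with no visit named. The same paragraph gives 8 weeks of treatment and then 2 weeks of observation, so week 10 is off treatment.
- **Statistical analyses:** the quantity analysed is "the degree of change of the VAS averaged after treatment from baseline". Groups are compared by a two-sample t test or a Wilcoxon rank sum test, with an additional analysis of covariance. For significance, a P value below "0.05 will be considered statistically significant". No multiplicity rule is given.
- **Sample size calculations:** "Under the assumption of 2.1 cm (with a pooled standard deviation of 2.4 cm) in the mean change difference in VAS values", "two-sided, and 0.05 of alpha", power 0.9, hence "28 participants will be allocated to each group". This is one difference, again with no visit named.

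**The concern.** The trial is presented as one that should confirm an antipruritic effect, so the reader must be able to tell in advance which result decides it. The endpoint section offers four candidates. The other sections suggest one, but do not say which visit or visits it uses. With a flat 0.05 threshold, nothing in the text prevents a favourable visit from being presented as the primary result, and after unblinding a chosen visit cannot be told apart from a planned one. At stake is whether the stated two-sided 5% is the error rate of the primary claim.

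The off-treatment visit is a separate difficulty. A change at week 10 answers a question about persistence after stopping, which is not the same question as the effect at the end of treatment.

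**Working it through.** **1. The plan's own figure.** Inputs from Sample size calculations: difference 2.1 cm, SD 2.4 cm, two-sided alpha 0.05, power 0.90, dropout 30%.

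n per group = 2 × (1.960 + 1.282)² × 2.4² / 2.1² = 27.4, rounded up to 28. Then 28 / 0.70 = 40 per group, 80 in total. Both figures reproduce. Exact noncentral-t power at 28 per group is 89.5%. The calculation is for one comparison at 0.05.

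**2. Error rate if any of four visits may count.** This success rule is an assumption; the article does not state it. The article also gives no between-visit correlation, so a range is needed.

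With independent tests: 1 − 0.95⁴ = 18.5%. With equal correlation r between the four test statistics, the chance of at least one |Z| > 1.960 under no effect is:

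| r | at least one P < 0.05 |
|---|---|
| 0 | 18.5% |
| 0.3 | 17.4% |
| 0.5 | 15.6% |
| 0.7 | 13.0% |
| 0.8 | 11.4% |
| 0.9 | 9.4% |

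**3. Narrowing the range for change scores.** All four changes subtract the same baseline. If raw VAS has variance σ² at every visit and the same correlation ρ between any two visits, then:

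- covariance of two changes = σ²(ρ − ρ − ρ + 1) = σ²(1 − ρ)
- variance of each change = 2σ²(1 − ρ)
- correlation = 0.5 whatever ρ is, giving 15.6%

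If the raw correlation instead decays with time (first-order autoregressive over weeks 0, 2, 4, 8, 10, with 2-week correlation 0.3 to 0.9), simulation gives 15.3% down to 13.5%. So about 14% to 16% holds under these shared-baseline models.

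**4. Error rate with one prespecified comparison.** One visit, or one defined average, tested once: 5%.

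**5. Cost of keeping all four visits primary.** Bonferroni is used as an example: 0.05 / 4 = 0.0125, with normal quantile 2.498.

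n per group = 2 × (2.498 + 1.282)² × 2.4² / 2.1² = 37.3, rounded up to 38; 38 / 0.70 = 54.3, rounded up to 55 per group, 110 in total. Exact noncentral-t power at alpha 0.0125 is 75.2% with 28 per group and 90.9% with 40 per group.

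**The case against.** The strongest reply is that the article elsewhere speaks of one comparison. The abstract has one difference, the sample size has one mean change, and the analysis section refers to the between-group difference in the singular. On that reading there is one test and the error is 5%. This stands as far as it goes: a single test is possible, and no any-visit rule is written down. But the article does not say which single test. The averaged VAS in the analysis section may be the 3-day mean defined for each visit, which still leaves four tests. It may instead be an average over visits, which is defined nowhere and, over the listed visits, would mix on-treatment values with week 10.

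A second reply is that an unseen analysis plan may settle the matter. That is fair for the primary analysis set, the choice between t and Wilcoxon tests, and the details of a multiplicity procedure; none of these is held against the article. The primary endpoint is different. The article does define it, over four visits, and that definition does not fit the single comparison for which the trial was sized.

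Four stronger readings are tempting and should be resisted:

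- **That the false-positive rate is 15%.** This needs both the unstated success rule and an assumed correlation.
- **That it reaches 24% to 27% once the t test, Wilcoxon test, covariance analysis and visit average each count as a way to win.** The text offers t or Wilcoxon as alternatives and the covariance analysis as an addition.
- **That power is 75% rather than 90%.** This holds only for Bonferroni with 28 analysed per arm. The full analysis set and last-observation-carried-forward could keep up to 40 per arm, where power is about 91%.
- **That the sample size was calculated for week 8.** That section names no visit.

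**Conclusion.** The point holds as a defect in how the primary endpoint is fixed. The endpoint section makes four visits primary, one of them off treatment, and names neither a decisive visit nor a multiplicity rule; the abstract and the sample size imply one unnamed comparison at two-sided 5%.

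The size is conditional. Under an any-visit success rule the error is about 9% to 18.5% for equal correlations from 0.9 down to 0, and about 14% to 16% under the shared-baseline models. Under a single prespecified comparison it is 5%. The documents do not establish which of these applies, and that uncertainty is the finding. Because the primary claim rests on it, it should be settled before any result is seen.

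**What to change.** Before unblinding, name one primary comparison and use the same wording in the abstract, the endpoint section, the sample size calculation and the statistical section.

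- **Natural choice:** the between-group difference in VAS change from week 0 to week 8, with weeks 2, 4 and 10 secondary. Week 8 is the end of treatment and the time point at which the article assesses its secondary endpoints. This is a recommendation, not something the sample size section already implies.
- **Equally adequate:** one average over the on-treatment visits, with those visits listed; or, if all four visits stay primary, a stated multiplicity procedure.

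With a single comparison the change is wording only: 28 evaluable per group and 80 in total are unchanged, and no extra data are needed. If Bonferroni over four visits is chosen, restate the power as about 75% at 28 evaluable per arm and about 91% at 40 per arm. The small downside of a single comparison is that a result at another visit can no longer be called primary.

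The article does not show whether the data are still blinded: recruitment was due to finish on 31 December 2018 and publication was in November 2019. If unblinding has already happened, report when the primary comparison was chosen.

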### Secondary and other endpoints

Total immunoglobulin E, eosinophil count, eosinophil cationic protein, phosphorus, calcium/potassium, intact parathyroid hormone, Kidney Disease Quality of Life, and Beck Depression Inventory will also be assessed between week 0 and week 8.

### Clinical and laboratory evaluations

Physical examination, comorbidity, and medication will be reviewed. Laboratory evaluations, including complete blood cell count, serum glucose, uric acid, total protein, albumin, total bilirubin, aspartate transaminase, alanine transaminase, alkaline phosphatase, blood urea, creatinine, total cholesterol, urinalysis, urine human chorionic gonadotrophin, and HIV status, will also be performed at visit 1.

### Safety assessment and adverse events

Information on adverse events (AEs) will be obtained through nondirective questioning to every participant at each visit. The safety assessments include laboratory tests (hematology/blood chemistry, urinalysis), electrocardiogram, chest x-ray, physical examination, blood pressure, pulse rate, and changes in body weight. At least once after randomization, any AEs that occur after administration of the investigational drug will be assessed. All AEs will be summarized and presented with regard to severity, relationship to the investigational drug, and outcome. The schedule of enrollment, interventions, and assessments is presented in Fig. 2.

**Fig. 2 Fig2:**
[figure not shown]
Timeline of study procedures and outcome assessments. BDI Beck Depression Inventory, Ca calcium, ECG electrocardiogram, ECP eosinophilic cationic protein, IgE immunoglobulin E, iPTH intact parathyroid hormone, K potassium, KDQoL Kidney Disease Quality of Life, P phosphorus, VAS visual analog scale

### Sample size calculations

The enrolled participants will be randomly divided into two groups by at a 1:1 ratio. Under the assumption of 2.1 cm (with a pooled standard deviation of 2.4 cm) in the mean change difference in VAS values between the PG102P and placebo groups in a preceding pilot study with 0.9 of power, two-sided, and 0.05 of alpha, 28 participants will be allocated to each group. Considering a dropout rate of 30%, 80 participants will be needed (40 participants per group).

### Data collection and management

All data will be recorded by trained clinical investigators from each participating hospital in a standardized electronic case report form using a web-based database (Bethesdasoft Co., Ltd., http://www.mytrial.co.kr). Data will be handled confidentially and anonymously by qualified data managers. Quality control will involve collecting data on adherence to the intervention, patient inclusion and follow-up, as well as monitoring the quality of the data entry. Missing data or inconsistencies in the data will be detected by programs, and the results will be reported back to the investigator for resolution. If any given case is missing a main variable, the results of the closest observation are carried forward to the absence of the test data (last observation carried forward). Through this iterative process, we will clean the data and finally perform a database lock. All database backups of the electronic case report form will be done in real time.

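### Last observation carried forward is the only stated rule for missing VAS although 30% dropout is allowed for, so the primary comparison can be diluted or biased and 90% power is not assured

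*Protocol article*

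**What the plan says.** Under Data collection and management, the protocol article states that for a missing main variable "the results of the closest observation are carried forward to the absence of the test data (last observation carried forward". It gives no other missing-data rule. The next sentence is "Through this iterative process, we will clean the data and finally perform a database lock".

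Under Sample size calculations: "Under the assumption of 2.1 cm (with a pooled standard deviation of 2.4 cm) in the mean change difference in VAS values", "with 0.9 of power, two-sided, and 0.05 of alpha", "28 participants will be allocated to each group". Then: "Considering a dropout rate of 30%, 80 participants will be needed", which is 40 per group.

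Under Statistical analyses, the full analysis set holds every randomized participant with at least one treatment. The groups are compared by a two-sample t test or rank sum test, with an additional analysis of covariance.

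Under Primary endpoint and measurement of itch, the endpoint is the VAS change from week 0 to weeks 2, 4, 8 and 10. Treatment ends at week 8. On visit spacing, Follow-up says: "Each interval between visits is 2 weeks, except that between visits 4 and 5 (which is 4 weeks".

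**The concern.** Carry-forward assumes that itch stays at its last recorded level after a participant leaves. If VAS improves over the 8 weeks, that assumption is wrong for every dropout, and a two-sample test then counts the filled value as a real measurement.

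Two consequences follow. With equal dropout, a developing drug effect is diluted. With unequal dropout, a general improvement shared by both arms (placebo response or regression to the mean) becomes a difference between arms that the drug did not cause. That second error can favour either arm, so it cannot be excused as conservative.

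The rule governs the primary endpoint of a trial that itself allows for losing three participants in ten. The Discussion argues for the efficiency of repeated measures, yet the stated comparison reduces the visits to one filled change score per participant.

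**Working it through.** **Inputs from the protocol article:** difference 2.1 cm, SD 2.4 cm, two-sided alpha 0.05, power 0.90, 28 evaluable per group, 30% dropout, 40 per group, VAS at weeks 0, 2, 4, 8 and 10.

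**Assumptions (not in the article):** the timing of dropout, the path of VAS over time, a between-visit correlation of 0.5, the improvement common to both arms, any imbalance in dropout, and week 8 as the time point of interest.

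**1. The plan's own figure.** n = 2 × (1.960 + 1.282)² × 2.4² / 2.1² = 2 × 10.51 × 5.76 / 4.41 = 27.4, so 28 per group. Inflated: 28 / 0.70 = 40. Both figures reproduce. Power at 28 per group is 0.906 (normal) or 0.895 (t).

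**2. Dilution with equal dropout.** 0.30 × 40 = 12 per arm carry a value. If carried values hold a share f of the full effect, the expected difference is 2.1 × (0.70 + 0.30f). With all 40 per arm analysed and the SD held at 2.4:

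| f | difference (cm) | power, normal | power, t |
|---|---|---|---|
| 0 | 1.47 | 0.78 | 0.77 |
| 0.25 | 1.63 | 0.86 | 0.85 |
| 0.50 | 1.79 | 0.91 | 0.91 |
| 0.75 | 1.94 | 0.95 | 0.95 |
| 1 | 2.10 | 0.97 | 0.97 |

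Break-even for 90%: the difference must be 3.242 × 2.4 × √(2/40) = 1.74 cm, so f = (1.74/2.1 − 0.70)/0.30 ≈ 0.43 (t: 1.76 cm, about 0.46).

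The SD need not stay at 2.4. At f = 0, treating each arm as a mixture of completers and zero-change dropouts gives power of 0.87, 0.83 or 0.75 for an assumed placebo improvement of 0, 1 or 2 cm.

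**3. Simulation over trajectories** (40 per arm, 30% dropout in each arm, last observed visit equally likely to be week 0, 2 or 4, common improvement 0 to 2 cm).
- Linear build-up to week 8: carried shares 0, 0.25 and 0.5, mean 0.25. Estimate 2.1 × 0.775 = 1.63 cm (22% smaller), power about 0.79 to 0.87.
- Linear, but every dropout has a week 2 or week 4 value: about 1.70 cm, power 0.82 to 0.87.
- Full effect by week 4, half of it at week 2: mean share 0.5, 1.79 cm, power about 0.89 to 0.93.
- Full effect by week 2: power 0.92 to 0.95.
- For comparison, completers alone: 2.1 cm, power about 0.89.

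**4. No drug effect, unequal dropout.** If both arms improve by m cm and carried values hold a share g of that change, the false difference is (difference in dropout) × (1 − g) × m. With 40% v 20% and g = 0.25:
- m = 2: 0.20 × 0.75 × 2 = 0.30 cm, type I error about 9%.
- m = 3: 0.20 × 0.75 × 3 = 0.45 cm, type I error about 12 to 13%.

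More dropout on active biases against the drug, and more on placebo biases in its favour. At 35% v 25% and m = 2, the false difference is 0.10 × 0.75 × 2 = 0.15 cm and type I error about 6%. With equal dropout the false difference is zero and type I error about 5%.

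**The case against.** The strongest reply is that the harm is conditional. The article gives no itch trajectory, no dropout timing and no sign that dropout will differ by arm. Carry-forward also returns 12 participants per arm to the analysis, and with an early effect its power exceeds that of completers alone. The higher type I error needs both a marked dropout imbalance and a large common improvement. All of this stands, and it limits the point to a risk.

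The time point is also open. The endpoint lists four visits, Statistical analyses refers to an average after treatment, and the 2.1 cm is tied to no visit. The week-8 figures above are therefore an illustration.

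Four stronger readings are tempting but not supported:
- *The trial will miss its 90% power.* Not shown: power runs from about 0.77 to 0.97 with the SD held at 2.4.
- *The sample size is wrong because dropouts return to the analysis.* No: 28 and 40 are correct, and sizing on evaluable participants while also analysing a fuller set is ordinary practice.
- *Imputed values will be locked as data.* The rule sits beside the cleaning and lock text, but the iterative process there most naturally means the query loop with investigators. Nothing says that filled values are written to the database.
- *A missing week 8 could be filled from week 10, off treatment.* Week 10 is indeed the nearer visit (2 weeks, against 4 weeks back to week 4). But *forward* and the bracketed term rule out a later value, so *closest* is loose wording.

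Sensitivity analyses may sit in an analysis plan that is not shown, so their absence is no fault here.

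**Conclusion.** The concern holds as a weakness in a stated rule. Carry-forward is the only missing-data method given, and it feeds up to about 12 of 40 values per arm into the primary comparison as if observed.

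With equal dropout it can shrink a 2.1 cm difference to about 1.6 cm. Power stays at 90% or above only if carried values hold roughly 43 to 46% or more of the effect (SD 2.4). The fair statement is that 90% is not assured.

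The false-positive risk of about 9 to 13% rests on 40% v 20% dropout with a common improvement of 2 to 3 cm. It nearly vanishes at 35% v 25% and is absent with equal dropout.

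This should be fixed. It does not by itself show that the trial's result would be wrong.

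**What to change.** - Replace the carry-forward sentence with a primary analysis by a likelihood-based repeated-measures model on the observed post-baseline VAS visits (treatment, visit, treatment-by-visit, baseline VAS as covariate), or by multiple imputation.
- Name the time point at which the treatment contrast is read. The endpoint lists weeks 2, 4, 8 and 10, so selecting week 8 or leaving out week 10 must be an explicit decision.
- Put the missing-data rule in the statistical section, and state that missing values stay missing at database lock.
- If carry-forward is kept, make it supplementary and change *closest* to *last*.

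The cost is a wording change and modest programming. No new data are needed, and the planned software can fit a mixed model. The downside is that such a model relies on data being missing at random, which the trial cannot verify.
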